### Outcomes

To achieve these aims, the following tests and measurement instruments will be included in the experimental set-up:

#### Motion analysis

3-D motion analysis will be used to answer the research questions 1 and 2 regarding the effects of upper body posture with and without the use of the exoskeleton during both tasks (*cf.* research question 1 b) as well as comparing both tasks under previous physical fatigue (2 b).

Motion analysis based on video recordings, and 3-D motion analysis via Xsens will be carried out.

Video recordings will take place to analyze participants’ body posture through a specified movement observation sheet and evaluation based on a scoring system [OWAS; (46)].3-D motion analysis will be performed via Xsens MVN 2018, a three-dimensional kinematic motion measurement system. The angular measures of the body (shoulder girdle, arms, wrists, upper and lower back, legs) are evaluated. Body movements are recorded via 17 inertial sensors that enable a three-dimensional analysis of the body segments in three dimensions (47).

#### Muscle activity

Muscle activity will be measured to address research questions 1and 2, which investigate the effects of using an upper body exoskeleton on muscle synergies during task performance, both in general (1b) and under conditions of prior physical fatigue (2b).

In the realm of biomechanical research, the analysis of muscle activity through surface electromyography (sEMG) is a pivotal methodology, particularly when scrutinizing the upper extremity muscles exposed to loading during overhead activities. This comprehensive investigation extends to an array of key muscles, especially in the context of upper extremity activities and overall body stability. The included muscles encompass *M. Biceps brachii*, *M. Triceps brachii caput longum*, *M. Brachioradialis* as prime movers of the forearm, as well as *M. deltoideus*, *M. pectoralis* major, *M. trapezius descendens*, *M. Latissimus dorsi* and *M. Infraspinatus* as movers around the shoulder. Ultimately the *M. rectus* abdominis will be included due to its role in postural stability. For the accurate measurement of muscle activity, adherence to the established guidelines is decisive. The “SENIAM Guidelines,” as articulated by Hermens et al. (48), outline the standardized protocols for non-invasive assessment. By following these guidelines, the research endeavors to ensure precision and reliability in the collection and interpretation of sEMG data, thereby advancing our understanding of the intricate interplay of muscles during dynamic upper extremity movements.

#### Muscle synergies

The methodology behind calculating muscle synergies is focused on analyzing sEMG data of muscles involved in multijoint movements. The aim is to build groups of synergistic muscles with distinct temporal activation patterns and individual muscle weightings. The method described to be most favorable to identify these groups is the non-negative matrix factorization of time-series data (23). The approach involves a comprehensive examination of muscle activity and their interactions during various physical activities.

#### Brain hemodynamics using fNIRS

Functional near-infrared spectroscopy (fNIRS) will be used to answer research questions 1 and 2, which investigate the effects of using an upper-body exsoskeleton on cognitive resources during task performance, both in general (1c) and under conditions of prior physical fatigue (2c).

Functional near-infrared spectroscopy (fNIRS) is a non-invasive, optical imaging technique for measuring brain activity in the cerebral cortex based on the interactions between neuronal activity, cellular metabolic processes, and increased blood flow (neurovascular coupling).

During cognitive, perceptual, and motor processes, there is increased neuronal activity in certain regions of the brain. As a result, there is an increased demand for energy and oxygen, which is met by the influx of oxygen-enriched blood. This leads to a relative increase in the concentration of oxygenated hemoglobin (O2Hb) compared to deoxygenated hemoglobin (HHb). To measure this change, infrared-emitting emitter diodes (transmitters) and light-sensitive detectors (receivers) are attached to the skull with a cap. The fNIRS measurement is based on the projection of infrared light (700–900 nm) from a source diode into the tissue under the scalp and the measurement of the intensity of the backscattered light with detectors. Due to the different optical properties, the concentration of O2Hb and HHb can be determined from the amount of backscattered light. By evaluating changes in oxygen consumption over time, conclusions can be drawn about the activity of cortical areas during the processing of certain tasks, emotional reactions and cognitive information.

#### Speed accuracy trade offs (Fitts task)

The Fitts task is a standard motor control experiment in which participants move quickly between two targets of different sizes and distances (44). The aim is to assess the speed and accuracy of the target movements. The difficulty of the task is determined by a difficulty index, which is calculated based on the size and distance of the targets. The researchers manipulate the task conditions to investigate factors that influence movement time and accuracy. Key measures include movement time and error rate, which provide insight into the trade-off between speed and accuracy in motor control. The Fitts task is often used in human-computer interaction and to assess motor skills.

The Borg rating of perceived exertion is used together with the SUS and the NASA-TLX questionnaires to answer research question 1d, investigating the effects of using an upper body exoskeleton on comfort/discomfort, acceptance and ease of use during task performance.

#### Subjective perceived exertion (Borg-scale)

The subjective assessment of the perceived exertion is carried out by using the 15-point Borg scale (6–20) after each test session. 6 points equal very very low exertion, and 20 points equal very very high exertion (49). The assessment refers to the overall perceived exertion and specific body regions, such as the neck, shoulders, arms, upper and lower back, and legs. A chart is shown for this purpose.

#### Subjective workload assessment questionnaire

The Subjective workload assessment questionnaire (NASA-Task Load Index, NASA-TLX) addresses the technical part of the experiment, capturing workload at multiple levels, regarding the interaction with the exoskeleton: mental demands, physical demands, time demands, performance, effort, and frustration (50).

#### System usability scale (SUS)

The System Usability Scale (SUS) provides a reliable tool for measuring usability. Comprising 10 questions with response options ranging from “Strongly Agree” to “Strongly Disagree.” This tool facilitates the assessment of diverse products and services, encompassing hardware, software, mobile devices, websites, and applications.

#### User acceptance

We have added a few questions on user acceptance. The topics of these questions are from Elprama et al. (51) and they are based on the framework of exoskeleton acceptance by Elprama et al. (52) with 5-point scale answers, mostly ranging from “Strongly Agree” to “Strongly Disagree.”

### Participant timeline

The study will be conducted over two separate days to mitigate potential carryover effects and ensure the avoidance of additional fatigue symptoms. On each day, participants will undergo the assigned conditions for both tasks in a randomized order, minimizing the impact of confounding variables. The sequence of conditions will be counterbalanced across participants to control for order effects.

First, the participants are welcomed and informed in writing and verbally about the aim and conduct of the study. This is followed by the recording of the anthropometric data and personal data. Then the preparations for the surface electromyography begin, including the application of the electrodes and the pre-tests (MVC). The suit for the Xsens sensors is then applied and a calibration is carried out. Finally, the sensor and the calibration for the fNIRS are carried out.

The first session then begins, depending on which task was selected first for the person. The person is then either fitted with the exoskeleton and begins the first task (Physical Performance Task or Precision Task) or performs this without the exoskeleton. If the fatigue protocol is already planned for the person at the beginning based on the randomization, this is carried out without the exoskeleton before the start of the task.

After completion of the first task, an individual break is taken before the second task begins. After completing both tasks, the person is asked to complete the questionnaires.

Due to the activity of overhead work, which already involves increased exertion because of the non-ergonomic posture, and the additional activity of screwing, physical fatigue may increase. Therefore, physical exertion is subjectively documented via the Borg scale (49) after each test session. Additionally, test sessions are spread over 2 days.

Individual breaks will be provided between each test session due to possible mental and physical exertion during the tests (Figure 3).

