### Exoskeleton being used

This study will conduct the experiments using the battery powered, pneumatic exoIQ (name of the company) S700 active Exoskeleton. The S700 is purposefully designed to support during manual tasks in and above shoulder height and is commercially available from 2023. It can be adjusted to fit both men and women from between 1.65 m up to 2.05 m body height and with various body types. Both, the amount of supporting torque and the characteristics of its application during use (torque curve) can be altered to the demands of user and task. These alterations are being stored on the device via presets. For each task, a specified preset will be used and the amount of support torque will be adjusted to the individual need.

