### Experimental set-up/intervention

The experimental design includes two physical tasks (1. Physical Performance Task and 2. Precision Task) in four randomized conditions (with and without exoskeleton and with and without prior physical fatigue; *cf.*
Figures 1, 2):

Physical Performance Task (PILE task) at shoulder height:Participants will perform the Physical Performance Task at shoulder height, both with and without the exoskeleton. This task aimed to assess the impact of the exoskeleton on physical performance under normal working conditions.

Precision Task (nailing following the Fitts paradigm) at overhead height:The Precision Task involves overhead nailing activities following the Fitts paradigm (43, 44) (three predefined templates into which the nails must be precisely inserted.), simulating tasks requiring precision and skill. Participants will execute this task with and without the exoskeleton, allowing the evaluation of the exoskeleton’s influence on tasks demanding fine motor skills.

Randomization will be done by the online program www.randomizer.org.

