#### Physical fatigue session

A fatigue session takes place, following a randomized order, e.g., before the PILE task or before the nailing task. The fatigue session will be performed in 3 sets, with a 2-min calf raise and a 2-min front raise with weight per set, with the front raise in the second set only being performed for the second minute. The weight of the men is 5 kg and that of the women 2.5 kg. There will be a break of 60 s between the sets. During the exercise, a metronome runs at 60 bpm, and the front and calf raises are to be performed to this beat. Before the start of the fatigue session, the maximum body height will be determined individually on the anthropometer by the test person standing upright and bringing their feet into plantar flexion. This determined height should be reached during each exercise. The level of fatigue will be determined using EMG power spectral shifts (Fast Fourier Transform) in combination with a visual analog scale of peripheral fatigue.

Questionnaires on acceptance and discomfort of the conditions with exoskeleton use will be filled out after the experimental procedure.

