### Fatigue effects

Regarding physical fatigue we suppose that firstly the overall gender effects might be reduced. One potential explanation lies in the idea that the additional required motor resources after fatigue will reduce the discomfort effect. According to fatigue it has to be assumed that the task management requires more muscle activity that can be reduced by the exoskeleton use (59). As this is relevant for both genders, the muscle activity and accompanying synergies might converge. Nevertheless, it is unclear if the weight of the exoskeleton affects muscle activity between men and women differently.

However, the organizing of body movement after fatigue needs more executive control in the motor cortex (60) and this will lead to less attentional resources available for the detailing recognition of the discomfort. This hypothesis will be proven by the analysis of the fNIRS data, regarding a potential shift from parietal to frontal cortex activation. This mechanism should be equal for male and female participants and might only be affected by age (61).

Moreover, as more resources for postural control and motor adjustments will be required after fatigue, the cognitive-motor interference in the DT condition will rise while movement accuracy will decrease. If the exoskeleton use will reduce this effect, it needs to be examined within our experimental design. On the other hand, the physical fatigue could also increase the proposed differences in upper body postures (more bending backwards of the women). This hypothesis would lead to increased muscle activity in the supporting muscles and might change muscle synergy patterns.

In summary, the knowledge of this study will contribute to refining and optimally implementing exoskeletons, with a focus on reducing fatigue and mitigating musculoskeletal risks, while considering the nuances of movement variability and cognitive resource allocation.

Furthermore, we would like to emphasize that the study also highlights the challenges, such as user discomfort and frustration, which can hinder the widespread adoption of this technology in real-world scenarios, especially for females.

The innovative focus lies on task and gender-specific variability including the muscle synergy approach. Analyzing muscle synergies can provide a nuanced understanding of muscle coordination and function, as well as the effects of interventions such as fatigue protocols or wearing an exoskeleton on these interactions.

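### Fatigued runs with the exoskeleton include a donning step between fatigue session and task that fatigued runs without it lack, and the visible text sets no common interval

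*Protocol article*

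**What the plan says.** Experimental set-up/intervention gives four conditions for each of two tasks: "with and without exoskeleton and with and without prior physical fatigue". Physical fatigue session describes the fatiguing exercise: "The fatigue session will be performed in 3 sets, with a 2-min calf raise and a 2-min front raise with weight per set". It times the rest inside the session ("There will be a break of 60 s between the sets") and says that the fatigue level is determined from EMG spectral shifts together with a visual analog scale.

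Participant timeline gives the order of events. On the exoskeleton: "The person is then either fitted with the exoskeleton and begins the first task"; the alternative is to do the task without it. On a fatigue protocol that randomisation places at the beginning: "this is carried out without the exoskeleton before the start of the task".

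Exoskeleton being used says that a preset is used for each task and that "the amount of support torque will be adjusted to the individual need", without saying when this is done.

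Fatigue effects, in the Discussion, states the expectation exposed to this point: after fatigue, "the task management requires more muscle activity that can be reduced by the exoskeleton use". It also leaves open, as something to examine, whether the device reduces the rise in cognitive-motor interference and the loss of accuracy after fatigue.

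**The concern.** The exoskeleton-by-fatigue contrast asks whether fatigue changes the outcomes less when the device is worn. That reading requires the same fatigue at the start of the task with and without the device. If donning takes place after the fatigue session, the participant recovers while it is done. Less residual fatigue would show as a smaller change in muscle activity, lower perceived exertion and better accuracy, which is also how a helpful device would look. The front raises in the fatigue session load the shoulder region, which is where the device gives support, so the recovery would fall where the benefit is expected.

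**Working it through.** **1. Order of events in the two fatigued runs, from Participant timeline**

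| Step | Fatigued, with exoskeleton | Fatigued, without exoskeleton |
|---|---|---|
| Fatigue session | done without the device | done without the device |
| Donning | required before the task | none |
| Task | starts after donning | no donning to wait for |

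The article does not say in so many words that the device goes on after the fatigue session. Its two statements leave no other order: the session is done without the device, and the task is begun with it. The sentence on fatigue concerns a session planned at the beginning; applying it to later sessions is an inference.

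**2. Is the gap equalised in the visible text?**

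The fixed rests are 60 s between fatigue sets (Physical fatigue session) and 30 s between templates (Precision task). Other breaks are individual. No interval from the end of the fatigue session to the start signal is given, and no matching wait in runs without the device.

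**3. Do the existing safeguards reach it?**

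Randomised and counterbalanced order and the spread over two days deal with order and carryover. The donning delay recurs in every fatigued exoskeleton run, whatever its place in the sequence, so averaging over sequences leaves it in. The fatigue check could reveal unequal fatigue if taken at task start, but its timing is not stated. If taken straight after the session, before donning, it would miss the difference.

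**4. Direction and illustrative size**

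The plan has no figure to reproduce. Assume fatigue decays exponentially with time constant tau. Let F be the fatigue effect on an outcome at the end of the session, g the gap common to both runs, and d the extra gap for donning. For a device that does nothing:

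- fatigue effect at task start without the device: F × exp(−g/tau)
- fatigue effect at task start with the device: F × exp(−(g + d)/tau)
- share that the device appears to remove: 1 − exp(−d/tau)

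The common gap g cancels, so the result does not require the run without the device to start at once. The document gives neither d nor tau. With assumed values:

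| d (min) | tau (min) | 1 − exp(−d/tau) |
|---|---|---|
| 0.5 | 10 | 1 − exp(−0.05) = 5% |
| 1 | 5 | 1 − exp(−0.2) = 18% |
| 2 | 5 | 1 − exp(−0.4) = 33% |
| 2 | 2 | 1 − exp(−1) = 63% |
| 5 | 2 | 1 − exp(−2.5) = 92% |

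The sign is the same in every row; the size ranges from trivial to dominant. These shares apply at task start. The tasks are themselves tiring and outcomes are recorded during them, so the shares are not the bias in the analysed contrast.

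**The case against.** The strongest objection is that the timing may exist where it cannot be seen. Figures 1 and 2 show the study flow of each task and Figure 3 the participants' time schedule; none is shown. A waiting time is also operational detail that an article may leave to the full protocol. This stands as a limit on confidence. It does not dispose of the point, because the stated order itself builds in the difference unless something equalises it.

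Several stronger readings are tempting, and the document does not support them.

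- *That all size and torque adjustment takes place after fatigue.* The time of adjustment is not stated, and settings are stored on the device as presets, so set-up beforehand is compatible with the text. Only donning follows from the stated order.
- *That the run without the device starts immediately.* The article does not say so.
- *That research question 2 is biased as it stands.* It asks about gender effects of exoskeleton use under prior fatigue, not whether the device lessens fatigue. A delay and a recovery that are the same in both genders drop out of that comparison.
- *That women take longer to fit, so the gender contrast is biased too.* Possible pitfalls and limitations speaks of commercial devices in general being hard to fit to some people, often women. It gives no donning times, and it expects this device's adjustment range and textiles to mitigate the problem.
- *That a substantial minimum bias can be stated.* With a short gap and slow recovery the share is about 5%.

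**Conclusion.** The point holds as a possible bias. Followed as written, the order of events gives fatigued exoskeleton runs a donning step, and so an opportunity to recover, that fatigued runs without the device lack. Unless the gap is equalised somewhere not shown, residual fatigue at task start may be lower with the exoskeleton, and the exoskeleton-by-fatigue contrast would then lean towards benefit. The size cannot be derived from the document; the illustrative 5% to 92% rests entirely on assumed gaps (0.5 to 5 min), assumed time constants (2 to 10 min) and exponential recovery. The gender contrast is affected only if donning time, or the fatigue recovered during it, differs by gender, and the document has no figures on either. Because the delay coincides with the condition, analysis after data collection cannot cleanly separate it from a device effect. Should-fix, with moderate confidence.

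**What to change.** State in the procedure, or confirm if the figures or the full protocol already do so:

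- One fixed interval from the end of the fatigue session to the start signal, the same with and without the exoskeleton and long enough for donning. In runs without the device the participant waits for the same time.
- Size and torque adjustment completed before the fatigue session, so that only donning remains afterwards.
- The actual interval recorded for every fatigued run.
- The existing fatigue check (EMG spectral shift and visual analog scale) taken right before task start in both kinds of run, so that equal fatigue can be shown rather than assumed.

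The cost is a few procedural sentences and a stopwatch. The small downside is that runs without the exoskeleton start with slightly less fatigue than if they began sooner.

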**Figure 3 fig3:**
[figure not shown]
Participants time schedule.

### Sample size

The sample size was calculated on the outcome of muscle activity using G*power (*a priori*, ANOVA with repeated measures and interaction effect) with 2 groups (male/female), 2 tasks (Physical Performance Task, Precision Task), 2 conditions (with/without exoskeleton), and 2 fatigue protocols (with/without fatigue protocol) estimating an effect size of 0.25, an alpha error rate of 0.05 and a statistical power of 0.80, resulting in *N* = 36 participants for each group. With an estimated drop of 20% we will include a total of *N* = 80 (40 female/40 male) healthy participants with male and female participants equally.

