**Methods:**

The cross-sectional study integrates a multifactorial mixed-measure design. Participants are grouped by gender (female vs. male) and working condition (with vs. without exoskeleton). Motor performance and underlying neuronal correlates (fNIRS) will be analyzed. Based on an *a priori* sample size calculation, 80 participants (40 female/40 male) will be recruited. Working performance will be assessed by 1. Physical Performance Task (PILE task) and 2. Precision Task (following the Fitts paradigm), while body postures will be monitored with an Xsens motion capture system. Brain activation will be captured with an fNIRS system comprising 32 active optodes. Postural comfort/discomfort, acceptance, and usability will be reported via standardized questionnaires.

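### Enrolling 80 covers 10% dropout, not the stated 20%: requirement, dropout rate and enrolment in the sample-size paragraph disagree

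*Protocol article*

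**What the plan says.** The Sample size section of the protocol article sizes the study on muscle activity ("The sample size was calculated on the outcome of muscle activity"). It uses G*Power for a repeated-measures ANOVA with an interaction effect. The design entered is "2 groups (male/female), 2 tasks (Physical Performance Task, Precision Task), 2 conditions (with/without exoskeleton), and 2 fatigue protocols", and the settings are given as "estimating an effect size of 0.25, an alpha error rate of 0.05 and a statistical power of 0.80". The stated result is "36 participants for each group", and the groups are male and female.

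The next sentence moves from requirement to enrolment: "With an estimated drop of 20% we will include a total of" 80, split 40 female and 40 male. The Methods part of the Abstract repeats the target, saying that "80 participants (40 female/40 male) will be recruited", and ties it to the a priori calculation.

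No other section gives a different dropout rate, a higher target or a rule for replacing participants who leave.

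**The concern.** Two consecutive sentences give a requirement, a loss rate and an enrolment figure, and the third does not follow from the first two. Because the 20% is introduced as the reason for enrolling 80, a reader will take 80 as the number that still leaves 36 per gender after a 20% loss. It does not.

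The paragraph's justification is at stake. If the authors' own dropout assumption proves right, the study ends with fewer participants than the paragraph says it needs, and the 80% power was attached to that larger number. Some loss is plausible: testing runs over two days, with surface EMG, motion capture and fNIRS recorded together, and the Data monitoring section foresees removing poor data.

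**Working it through.** **Inputs, all from the Sample size section:** requirement 36 per gender (72 in all); dropout d = 0.20; enrolment 40 per gender (80 in all); effect size 0.25, alpha 0.05, power 0.80.

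**1. Try to reproduce 40 per gender from 36 and 20%.**
- Usual formula, n / (1 − d): 36 / 0.80 = 45 per gender, 90 in all.
- Looser formula, n × (1 + d): 36 × 1.20 = 43.2, rounded up to 44 per gender, 88 in all.

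Neither gives 40.

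**2. Work forward from the enrolment.**
- 40 × (1 − 0.20) = 32 per gender, 64 in all.
- Shortfall: 36 − 32 = 4 per gender, 72 − 64 = 8 in all (8 / 72 = 11%).

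**3. Find the loss that 80 does absorb.** 1 − 36/40 = 1 − 72/80 = 0.10, so the allowance present is 10%.

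**4. Ask what 64 completers would mean for power.** This needs assumptions the article does not state: that 0.25 is Cohen's f, that the test is the gender-by-within interaction with two groups, and values for the number of measurements m and their correlation ρ. No correction for nonsphericity is applied. Under G*Power's default definition the noncentrality is λ = f² × N × m / (1 − ρ), with (m − 1) and (N − 2)(m − 1) degrees of freedom.

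Example: N = 64, m = 2, ρ = 0 gives λ = 0.0625 × 64 × 2 = 8 on 1 and 62 df, and power 0.795.

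| m | ρ | Power at 64 | Power at 72 |
|---|---|---|---|
| 2 | 0 | 0.795 | 0.841 |
| 2 | 0.3 | 0.914 | 0.942 |
| 2 | 0.5 | 0.976 | 0.987 |
| 4 | 0 | 0.929 | 0.956 |
| 4 | 0.3 | 0.986 | 0.994 |
| 8 | 0 | 0.994 | 0.998 |

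Higher correlations raise power further. One setting falls below 0.80 at 64, by half a percentage point.

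**5. Ask whether 36 per group itself can be recovered.** None of these two-group interaction settings gives 72. With ρ from 0 to 0.7, the total required is 22 to 66 for two measurements, 16 to 46 for four and 10 to 30 for eight. Other entries come close to the printed number:
- G*Power's SPSS-type effect-size option, two groups and eight measurements: 36 in total (power 0.803). The same option gives 62 in total with four measurements and 130 with two.
- A gender main effect, eight measurements, ρ = 0.5: 74 in total, or 37 per group.

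The base figure therefore cannot be confirmed, and the required total depends heavily on settings that are not reported.

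**The case against.** The strongest reply is that the discrepancy need not matter. The enrolment does contain an allowance, half of the one announced. Under the stated two-group interaction and the default effect-size definition, 64 completers exceed 80% power in every setting in the table except one, which misses by half a point. The figure of 36 may even be a G*Power total printed as a per-group number; 64 would then be ample. The Harms section also lets a session stopped for exhaustion or discomfort be repeated on another day, which may reduce loss. This is a laboratory study in healthy volunteers, and no test or design element changes.

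Most of this stands, and it limits the point. A reader might infer that no dropout allowance was made; that is wrong, since the step from 36 to 40 covers 10%. A reader might also infer that the study will miss 80% power. The documents do not support that either. A fall to about 75% can be calculated, but only by assuming that 72 gives exactly 80% on a test with one numerator degree of freedom, which none of the two-group interaction settings does. Treating the design as eight groups with two measurements (ρ = 0.5) gives 0.853 at 72 and 0.793 at 64, but it departs from the two groups the article names.

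The reply does not remove the contradiction. Repeating a stopped session is not a rule for replacing dropouts, and recruitment by snowball sets no higher target. If 36 is a misprinted total, the paragraph is still wrong, in a different place.

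**Conclusion.** The point holds as an internal inconsistency. A requirement of 36 per gender, a 20% loss and an enrolment of 40 per gender cannot all be true: 80 covers 10%, and at 20% there remain 64 completers against a stated need of 72. This part rests only on the printed figures and on reading "participants for each group" as each gender, which is what the text says.

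The 80% power is therefore not supported by the paragraph as written. Whether power would actually fall below 80% at 64 cannot be determined without the correlation, the number of measurements, the effect-size option and the effect tested. Nor can it be told which of the printed figures is the misreported one.

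**What to change.** First go back to the saved G*Power output. Confirm whether 36 is a per-group number or a total, which effect and settings produced it, and whether 20% is the intended dropout rate. Then restate the paragraph so that the figures agree, in whichever of these ways is true:

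- If 36 per gender is right and 80 stays, say that 80 allows for 10% dropout, leaving 72 completers.
- If 20% is right and 80 stays, say that 64 completers (32 per gender) are expected, and give the power or smallest detectable effect at 64 with the settings used.
- If the base number was misreported, correct it and redo the dropout step from the corrected figure.

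Keeping both 36 per gender and 20% would mean enrolling 90. That is needed only if the authors confirm both figures and want both to hold.

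The first three options cost a check of existing output and about one sentence of text. The downside is that the stated dropout tolerance or power may become slightly less favourable.
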